### Fidelity Tracking and Application of RE-AIM

MPACT fidelity tracking will assess the degree to which clinics assigned to the intervention arm implement MPACT components. This will be evaluated by a fidelity tracking instrument and video conversations with the clinic champions—biweekly during the pilot study and monthly during the trial period. A fidelity tracker will first be populated with data from study databases, including accredited training completion, TICA survey participation (number and ratio of staff completing surveys), number of anonymous wellness self-screenings, and reflective supervision participation (number of staff by role per biweekly session). During fidelity conversations, the clinic champion will indicate the number of wellness trainings offered to staff (current or new staff) in the past 2 weeks, whether posters for the wellness screener were shared in the staff-only areas, and whether there were other issues raised by staff about MPACT participation that may require troubleshooting.

MPACT feasibility will be measured through fidelity tracking (what the clinic does and does not implement and the feedback about issues related to that) and through items measured in the staff survey. The RE-AIM framework will guide the assessment of reach, adoption, implementation, effectiveness, and maintenance. Reach is focused on staff and patient participants in the MPACT study. Measures of reach include the number and proportion of clinics participating in the study (number participating/number in recruitment sample) and the number and proportion of staff and patients participating by the study clinic. Adoption is focused on the participation in MPACT intervention overall and by the MPACT component. This is measured by reported staff participation through the surveys and through completion data gathered through the intervention components. Examples include accredited training completion or progress toward completion, reflective supervision participant reports, and wellness assessment completion reported through study surveys and through wellness screening data output (duplicated unless noted by the participant by selecting “I have taken this assessment before,” and if selected, the participant can select the number of times the assessment has been completed prior). Implementation is measured through the fidelity check meetings with champions and reported MPACT activity (such as posting flyers about particular intervention components). Effectiveness is measured by primary and secondary outcomes related to the aims of this study. Maintenance will not be measured in the pilot study (4-month period) but will be measured through a survey conducted 6 months after the conclusion of the trial period.

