#### Staff Wellness Education and Assessment

All staff in MPACT-enrolled clinics will receive training about trauma exposure and reactions, trauma-informed methadone treatment, availability and modalities of trauma treatment, and VT through curated presentation materials. These materials will be accessible to all staff through an MPACT web portal and through training or communications as determined by the enrolled clinics. The training materials include video and visual content designed for easy integration into clinic employee training, onboarding, or as refresher training. As part of the training, staff will be introduced to an anonymous web-based “wellness” screener, which includes an 8-item posttraumatic stress disorder symptoms screener (Posttraumatic Stress Disorder Checklist [PCL-5]) [35,36] and an 8-item Vicarious Trauma Scale [37]. Individual screening outcomes (results) trigger a curated and immediately presented message regarding self-care, referral to the VA PTSD Coach [38,39] (a downloadable, free application) and referral to the employee assistance program offered as a behavioral health benefit to employees where indicated. Employees will have access to wellness training throughout the MPACT intervention period and can use the self-screener repeatedly if desired. The screener will also be “advertised” in staff-only areas with a curated poster on stress, including a link or QR for easy access.

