Other individual-level variables of interest for the staff participants include (1) personal characteristics—demographics, personal substance use disorder and treatment experience, and trauma exposure history (measured by the Life Events Checklist-5) [48]; (2) work characteristics—training, education, and licensure related to their clinic role; (3) empowerment using a 5-item empowerment scale [49]; (4) stigma—toward people with OUD with a 9-item scale [50], self-stigma with a 9-item scale [51], and fear of enacted stigma through a 9-item scale [52]; (5) beliefs—about trauma-informed care measured by the attitudes toward trauma-informed care [53] and about abstinence measured by the Abstinence Orientation Scale [54]; (6) comfort with targeted practices related to the most recent federal changes to methadone treatment delivery measured by items adapted from prior studies measuring comfort with practices [34,55,56]; and (7) fidelity to MPACT—the degree to which the clinic implements the MPACT intervention.

Other individual-level variables of interest for the patient participants include (1) personal characteristics—demographics, housing, trauma history (Life Events Checklist-5), and trauma symptoms (PCL-5); (2) methadone treatment—time in treatment and dose sufficiency; (3) empowerment—as measured by a 15-item scale [57] and through an adapted 16-item Kim Alliance Scale [58]; and (4) fidelity to MPACT—the degree to which the clinic implements the MPACT intervention.

As this is a hybrid (implementation and effectiveness) pilot and trial, we are specifically focused on reach, implementation, adoption, and (in the trial) maintenance using the RE-AIM (Reach, Effectiveness, Adoption, Implementation, and Maintenance) framework [59]. Measures collected for the pilot will also be collected for the trial.

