### Phase 2, Years 3-6: Hybrid, Cluster Randomized Controlled Trial

#### Overview

Aim 4: Quantify the effects of MPACT on methadone treatment practice change and clinic culture.Aim 5: Determine the efficacy of MPACT on methadone treatment retention and patient and staff PTSS outcomes.Aim 6: Evaluate the effect of patient and staff trauma on primary outcomes and staff MPACT implementation.

Findings from the pilot study will determine the preliminary effect size to confirm power analyses and final sampling for a hybrid type 1, 20-month cluster randomized controlled trial among 30 clinics, 600 patients (20 per clinic), and 480 staff (18 per clinic). This hybrid type 1 trial will focus primarily on MPACT’s effect outcomes while examining the association of MPACT implementation fidelity and acceptability and identifying the multilevel factors influencing implementation.

For the trial, the clinic is the unit of randomization. The intervention condition will be the MPACT intervention, and the control condition will involve accredited training about methadone that does not overlap aspects of the MPACT intervention. As shown in Table 2, we will allow a 20-month study period to accommodate staggered trial initiation through month 12 of year 2. Given the 20-month trial period, we will allow for new staff members to enroll through the end of the 7th month of their site’s trial period.

**Table 2 table2:** Cluster randomized controlled trial of Methadone Patient Access to Collaborative Treatment.

	Year 1			Year 2			Year 3			Year 4	
	Half 1	Half 2	Half 1		Half 2	Half 1		Half 2	Half 1		Half 2
Intervention arm clinics (n=15)	Start-up	Intervention	Intervention		Intervention	Intervention		Intervention	Intervention		Closeout
Control arm clinics (n=15)	Start-up	Usual care	Usual care		Usual care	Usual care		Usual care	Usual care		Closeout
Key processes	Randomization process finalized	Trial allows for staggered starts based on recruitment	Trial allows for staggered starts based on recruitment		Trial allows for staggered starts based on recruitment	Trial follow-up		Trial follow-up	Trial follow-up		Trial outcome analyses and dissemination

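### In the trial, the wellness-training count is asked monthly but looks back only 2 weeks, so this one fidelity item misses about half of the trial period

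*Protocol article*

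**What the plan says.** The section Fidelity Tracking and Application of RE-AIM describes two sources of fidelity data.

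- **Study databases.** "A fidelity tracker will first be populated with data from study databases". The feeds listed are accredited training completion, TICA survey participation, the number of anonymous wellness self-screenings, and reflective supervision attendance.
- **Video conversations with the clinic champion.** These are held "biweekly during the pilot study and monthly during the trial period". In them, "the clinic champion will indicate the number of wellness trainings offered to staff (current or new staff) in the past 2 weeks". The champion also reports whether the screener posters were displayed and whether staff raised other issues.

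The conversation content is described once, for both phases. The Measures section adds: "Measures collected for the pilot will also be collected for the trial". The description of the wellness component says: "Employees will have access to wellness training throughout the MPACT intervention period". Clinics decide how the material is delivered, and its uses include onboarding and refresher training.

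On the use of these data, the fidelity section says: "Implementation is measured through the fidelity check meetings with champions and reported MPACT activity". The Phase 2 Overview describes the hybrid type 1 trial as "examining the association of MPACT implementation fidelity and acceptability".

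**The concern.** A count collected at repeated contacts is complete only if each look-back reaches to the previous contact. The pilot meets this condition. The trial lengthens the interval to a month, but the only stated look-back stays at 2 weeks. Any wellness training held in the earlier part of the month falls outside every question asked.

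Wellness education is one of the four MPACT components, and the number of trainings offered is the item that shows whether a clinic delivers it as training. If about half of the period is unseen, recorded delivery is too low. A clinic that regularly trains soon after each conversation would look as if it did not train at all. Fidelity is tracked in the 15 intervention clinics only, so a few misplaced clinics can distort a description of implementation.

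**Working it through.** The article states no coverage figure to reproduce, so the check compares the stated window with the stated interval.

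**Inputs**
- Look-back window: 14 days (Fidelity Tracking section).
- Contact interval: 2 weeks in the pilot and monthly in the trial (same section).
- Trial period: 20 months (Phase 2 Overview). At 365.25/12 = 30.44 days per month, this is 20 × 30.44 = about 609 days.
- Assumption: monthly means a calendar month. The 4-weekly reading is shown as well.

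**Share of each interval not covered = 1 − 14/L, where L is the interval in days**

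| Interval | Covered | Not covered |
|---|---|---|
| Pilot, L = 14 | 100% | 0% |
| Trial, L = 28 (4-weekly) | 50.0% | 50.0% |
| Trial, L = 30 | 46.7% | 53.3% |
| Trial, L = 30.44 | 46.0% | 54.0% |
| Trial, L = 31 | 45.2% | 54.8% |

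**Over the whole trial period**
- 20 conversations × 14 days = 280 days covered. 609 − 280 = 329 days are not covered, and 329/609 = 54.0%.
- 19 conversations: 266 days covered, 56.3% not covered.
- 21 conversations: 294 days covered, 51.7% not covered.

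**What this does to the count.** Take, as an illustration, a clinic that holds one training a month, 20 in all.
- If trainings fall at random within the interval, the expected recorded number is 20 × 0.46 = 9.2.
- If they always fall in the 2 weeks before the conversation, all 20 are recorded.
- If they always fall earlier in the month, none is recorded.

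The two fixed-slot cases are extremes. They show that no constant multiplier can repair the count, because the error depends on each clinic's calendar.

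**How well recorded totals would track true totals.** Assume that trainings occur at random times, with mean m per clinic, between-clinic standard deviation t in the true rate, and covered share p = 0.46. The correlation between recorded and true totals is then r = √[p(m + t²)/(m + p·t²)]. The documents give neither m nor t; m = 20 is an assumption.
- t = 0 (all clinics share one rate): r = √0.46 = 0.68.
- Coefficient of variation 0.25, t = 5: r = √[0.46 × 45/(20 + 0.46 × 25)] = √(20.7/31.5) = 0.81.
- Coefficient of variation 0.5, t = 10: r = √[0.46 × 120/(20 + 0.46 × 100)] = √(55.2/66) = 0.91.

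The more clinics truly differ, the less random timing disturbs their ranking. The level stays about halved in every case.

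**Other sources.** None of the listed database feeds counts wellness trainings offered; self-screenings record use of the screener, not delivery of training. The staff survey items on MPACT practices and the component completion data concern staff exposure and participation, and neither is described as a clinic-level count of trainings offered.

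**The case against.** The strongest reply is that the 2-week phrase is pilot wording that was not adapted. It sits in a section covering both phases, ahead of the Phase 2 heading, and it matches the pilot cadence exactly. No sentence says that the trial conversation keeps a 2-week recall, and the fidelity instrument itself is not shown. The statement that pilot measures carry over to the trial does not mention recall windows. This reading is plausible, but it does not remove the mismatch: the article states both the interval and the look-back, and gives no other look-back for the trial.

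Several stronger readings are tempting and should not be drawn:

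- **That fidelity as a whole goes half unrecorded.** The database items have no 2-week limit, and the poster and staff-issue items have no stated window.
- **That the missed trainings are certainly recorded nowhere else.** The list of database feeds is given as examples, and staff surveys and completion data bear on exposure to the component. What can be said is that no other stated source counts trainings offered.
- **That a planned analysis of fidelity against outcome is compromised.** The Phase 2 Overview names no outcome in that clause, and the Statistical Analysis section contains no such model.
- **That a pilot-versus-trial comparison of fidelity would be biased.** None is planned.
- **That recorded and true totals correlate at only 0.68.** This requires every clinic to have the same true training rate.

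It is also fair to say that undercounting by the same proportion everywhere would leave the expected ranking of clinics unchanged. That holds only if training dates are unrelated to conversation dates, and the article leaves delivery of the training to the clinics.

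**Conclusion.** The point holds for one item. With monthly conversations and a 2-week look-back, the trial's count of wellness trainings offered would miss about 54% of the trial period under calendar months (51.7% to 56.3% for 21 to 19 conversations), or 50% if conversations are every 28 days. This assumes that the stated look-back is applied in the trial as written.

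The consequence is a weaker RE-AIM implementation measure for one of the four MPACT components. The size of the distortion cannot be fixed from the documents, because it depends on training dates and on true differences between clinics. The primary and secondary outcomes and the power are untouched, and no between-arm comparison is biased, because fidelity is tracked only in the intervention arm. It is a modest point, but the mismatch is plain on the page and is best corrected before the trial's first fidelity conversations, since missed periods may be hard to reconstruct later.

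**What to change.** For the trial, replace the fixed 2-week look-back with the number of wellness trainings offered since the last fidelity conversation. Record the date of each conversation, so that the observed time is known when one is late or skipped, and report trainings per month of observed time. For a clinic's first conversation, count from the MPACT launch at that clinic. Coverage then rises from about 46% to 100% of each interval. The same wording serves the pilot definition, where the interval is already 2 weeks.

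The change is one phrase and one date field in the fidelity instrument. The downside is that the champion must recall about a month instead of 2 weeks, which may add some recall error.

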### Phase 2, Years 3-6: Hybrid, Cluster Randomized Controlled Trial

#### Overview

Aim 4: Quantify the effects of MPACT on methadone treatment practice change and clinic culture.Aim 5: Determine the efficacy of MPACT on methadone treatment retention and patient and staff PTSS outcomes.Aim 6: Evaluate the effect of patient and staff trauma on primary outcomes and staff MPACT implementation.

Findings from the pilot study will determine the preliminary effect size to confirm power analyses and final sampling for a hybrid type 1, 20-month cluster randomized controlled trial among 30 clinics, 600 patients (20 per clinic), and 480 staff (18 per clinic). This hybrid type 1 trial will focus primarily on MPACT’s effect outcomes while examining the association of MPACT implementation fidelity and acceptability and identifying the multilevel factors influencing implementation.

For the trial, the clinic is the unit of randomization. The intervention condition will be the MPACT intervention, and the control condition will involve accredited training about methadone that does not overlap aspects of the MPACT intervention. As shown in Table 2, we will allow a 20-month study period to accommodate staggered trial initiation through month 12 of year 2. Given the 20-month trial period, we will allow for new staff members to enroll through the end of the 7th month of their site’s trial period.

**Table 2 table2:** Cluster randomized controlled trial of Methadone Patient Access to Collaborative Treatment.

	Year 1			Year 2			Year 3			Year 4	
	Half 1	Half 2	Half 1		Half 2	Half 1		Half 2	Half 1		Half 2
Intervention arm clinics (n=15)	Start-up	Intervention	Intervention		Intervention	Intervention		Intervention	Intervention		Closeout
Control arm clinics (n=15)	Start-up	Usual care	Usual care		Usual care	Usual care		Usual care	Usual care		Closeout
Key processes	Randomization process finalized	Trial allows for staggered starts based on recruitment	Trial allows for staggered starts based on recruitment		Trial allows for staggered starts based on recruitment	Trial follow-up		Trial follow-up	Trial follow-up		Trial outcome analyses and dissemination

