#### Reflective Supervision Consultation

Reflective supervision is an evidence-based professional development intervention focusing on the relationship and process of collaborative case consultation and reflection for clinicians providing psychosocial support [41,42]. Reflective supervision provides strategic guidance to increase self-reflectiveness and self-awareness and encourages participants to independently process clinical encounters and solve challenges. These skills have been shown to improve patient care [43,44]. To our knowledge, there are no existing reflective supervision consultation models tailored to OTP staff. Therefore, we adapted the standard reflective supervision practices to apply and be accessible to all OTP staff who have intensive and consultative interactions with patients. These staff roles include case managers, counselors, and peer support. Reflective supervision will begin in month 1 of the intervention period and will continue on a biweekly basis throughout the intervention period for each MPACT-enrolled clinic. Sessions are facilitated by a trained reflective supervisor who will also be trained by the MPACT study clinician.

Aim 2: Determine MPACT implementation feasibility, acceptability, and preliminary effect on methadone treatment practice change and clinic culture.Aim 3: Determine the preliminary effect of MPACT on methadone treatment retention and patient PTSS.

A single-arm 5.5-month pilot study of MPACT will address aims 2 and 3 and involves 2 Arizona-based OTPs (1 rural and 1 urban), 100 patients, and 22 staff (25 patients and 6 staff of the rural clinic and 75 patients and 16 staff of the urban clinic). Data collection will be accomplished through a web-based survey of staff and patient participants monthly during the pilot study period, which began in October 2024 and ended in March 2025. The 4 elements of MPACT intervention were delivered during the 4-month period following study recruitment. Eligibility criteria for study inclusion included being 18 years of age or older, being a staff member or a patient at 1 of the 2 pilot clinics, being willing to participate in monthly surveys during the pilot study period, and (for patients) agreeing to share selected components of their medical charts with the study team.

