### Measures

The primary study outcome is increased patient methadone treatment retention. This outcome is measured in three ways: (1) time to first treatment interruption, calculated as the number of days to first missed dose from day 0 (MPACT enrollment); (2) evidence of being active in treatment, a binary (yes or no) if receiving dose at points in time on day 0, 30, 60, 90, and 120; and (3) continuous days in treatment during the study period, calculated as time (days) to discharge. Data measuring this outcome are gathered by patient surveys and chart reviews.

Secondary study outcomes include reductions in VT and PTSS among enrolled clinic staff and PTSS among enrolled patients. Data measuring secondary outcomes are gathered by a survey of staff and patients enrolled in the study. For staff and patients, PTSS are measured using the 8-item posttraumatic stress disorder symptoms screener otherwise known as the PCL-5 [35]. Staff VT is measured by the Vicarious Trauma Scale [37], burnout is measured by a 3-item scale [45], and compassion satisfaction and compassion fatigue are measured by the shortened, 9-item Professional Quality of Life Scale for staff [46].

The degree to which methadone treatment is patient-centered is also a secondary outcome measured through staff surveys (assessing whether they believe they are providing it) and patient surveys (assessing whether they feel they are experiencing it). Patient-centered care competency is measured by a 19-item scale [47] including the following subscales: respecting patient perspectives, promoting patient involvement in the care process, providing patient support, and advocating for patients. Patient-centered care, as defined by the study team, is measured using a 5-item instrument that reflects the concepts of patient-centered care introduced during the accredited training modules. This scale is administered to staff, with an adapted version used for patients.

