### Statistical Analysis

Our primary outcome is patient time to first treatment interruption (confirmed in the pilot). Secondary outcomes include treatment retention (yes or no) at selected time points (1, 3, 6, and 12 months) and time to treatment discontinuation. To accommodate the clustering induced by nesting patients within clinics, we will use a mixed effects Cox proportional hazards model (shared frailty model) [61,62] to accommodate differential survival probability among clusters. The mixed model will include a random intercept for the clinic and a fixed treatment effect for MPACT or control assignment. We will also include patient-level covariates for age, sex, and time in MMT.

Our initial sample size calculation uses asymptotic normal results for log hazard ratio as well as sample size inflation factors (eg, Donner) [62] for cluster randomized trials. In designing the future R33 trial, we will make use of specific sample size methods for cluster randomized trials with time-to-event outcomes [63,64]. The relative frequency of first treatment interruption [65] is estimated as 66% at 12 months of MMT until we have confirmation from the pilot. We evaluate the number of clinics and number of patients, assuming that MPACT intervention reduces this frequency to 45% (n=240), 50% (n=300), and 55% (n=330). The power curves based on independent observations (no cluster effect) are shown in Figure 3. The graph shows that the recruitment of 30 clinics, with 20 patients per clinic, provides greater than 80% power to detect a difference in treatment interruption rates of 66% (control) and 55% (MPACT) with α=.05. Consistent with the cluster randomization trial design, we also consider the average number of patients per clinic as 10, 20, and 40 and different degrees of intraclinic clustering using intraclass correlation coefficients of 0.05 and 0.10.

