## Discussion

The MPACT study will provide a foundation for an evidence-based, staff-level intervention aimed at improving patient retention in MMT. We anticipate a decrease in reported levels of VT and PTSS among staff and an increase in methadone treatment retention among patients. The pilot outcomes are focused primarily on implementation with a preliminary indication of impact or effectiveness. The preliminary outcomes from the pilot will inform the final sampling to properly power the study. The trial outcomes are focused both on the implementation and effectiveness of the MPACT intervention. Future studies should examine the individual components of MPACT to determine their differential contributions to the primary outcome of patient MMT retention and to secondary outcomes of staff and patient reduction in stress symptoms.

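### A single-arm, two-clinic pilot followed to about day 120 should not determine the trial's effect size or confirm its 66% control interruption rate

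*Protocol article*

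**What the plan says.** Three places in the protocol article give the pilot a role in sizing the trial.

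- Phase 2, Overview: "Findings from the pilot study will determine the preliminary effect size to confirm power analyses and final sampling".
- Statistical Analysis: the frequency of first treatment interruption "is estimated as 66% at 12 months of MMT until we have confirmation from the pilot". The power statement that follows uses 66% as the control rate, against assumed MPACT rates of 45%, 50% and 55%.
- Discussion: "The preliminary outcomes from the pilot will inform the final sampling to properly power the study".

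The pilot is described at the end of the Reflective Supervision Consultation section, under Aims 2 and 3: "A single-arm 5.5-month pilot study of MPACT will address aims 2 and 3 and involves 2 Arizona-based OTPs (1 rural and 1 urban), 100 patients". The split is "25 patients and 6 staff of the rural clinic and 75 patients and 16 staff of the urban clinic". On exposure: "The 4 elements of MPACT intervention were delivered during the 4-month period following study recruitment". Measures defines being active in treatment as "a binary (yes or no) if receiving dose at points in time on day 0, 30, 60, 90, and 120", and the RE-AIM section calls the pilot a 4-month period.

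Data Collection says that chart review covers each enrolled patient from the start of treatment at the clinic. Results says that the pilot ended in March 2025, that its findings are being analyzed, and that the trial starts in December 2025.

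**The concern.** A two-arm trial is sized on a control event rate and a contrast between arms. The pilot has no untreated arm, so its follow-up gives no MPACT-versus-control hazard ratio. Both clinics received MPACT, so the interruption rate seen after enrolment is an exposed rate, whereas 66% stands for the control arm. Retention is followed for about a third of the 12-month horizon to which 66% refers. With two clinics, the estimate is also imprecise once clustering is allowed for.

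At stake is the final sample size. If the stated rule is followed, a target effect or control rate could be changed, or declared confirmed, on a number that does not estimate it.

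**Working it through.** **1. The plan's own figure.** Inputs (Statistical Analysis): 66% vs 55%, 600 patients, α = 0.05 (two-sided assumed), independent observations. Allocation is 15 vs 15 clinics (Table 2).
- Hazard ratio = ln(1 − 0.55)/ln(1 − 0.66) = 0.740.
- Events = 600 × (0.66 + 0.55)/2 = 363.
- Power = Φ(√363/2 × |ln 0.740| − 1.96) = Φ(0.91) = 81.8%.

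The stated power above 80% reproduces without clustering. The arithmetic of the present sizing is not at issue.

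**2. What sizing needs and what the pilot follow-up gives.**

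| Needed | Pilot follow-up |
|---|---|
| MPACT vs control contrast | one arm, no concurrent control |
| Control interruption rate | rate under MPACT |
| Rate at 12 months | retention to about day 120 |
| Precision enough to separate 66% from 55% | 100 patients in two clinics |

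**3. Moving the 12-month rates to day 120.** Assumption: constant hazard.
- Control: 1 − 0.34^(120/365) = 29.9%.
- MPACT: 1 − 0.45^(120/365) = 23.1%.
- Gap: 6.8 points.

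**4. Precision of the pilot rate.** Assumption: the trial's ICCs of 0.05 and 0.10 apply to the pilot.
- Size-weighted mean cluster size = (25² + 75²)/100 = 62.5.
- Design effect = 1 + (62.5 − 1) × ICC = 1, 4.08 and 7.15 at ICC 0, 0.05 and 0.10.
- 95% half-width = 1.96 × √(0.299 × 0.701/100 × design effect).
- 12-month value of each limit = 1 − (1 − limit)^(365/120).

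| ICC | Half-width (points) | 95% CI at day 120 | Same limits at 12 months |
|---|---|---|---|
| 0 | 9.0 | 20.9–38.8% | 51–78% |
| 0.05 | 18.1 | 11.8–48.0% | 32–86% |
| 0.10 | 24.0 | 5.9–53.8% | 17–91% |

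Even the narrowest interval contains both 66% and 55%.

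**5. Sensitivity to hazard shape.** Take 30% interrupted at day 120 and Weibull shapes k from 0.5 to 1.5 (assumed). The 12-month rate is 1 − 0.70^((365/120)^k): 46% at k = 0.5, 66% at k = 1 and 85% at k = 1.5. This spread comes on top of the sampling error in step 4.

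**6. Sensitivity to pilot length.** If follow-up ran the full 5.5 months (about 165 days), the constant-hazard rates would be 38.6% and 30.3%, a gap of 8.3 points. The independent-observations half-width would be 1.96 × √(0.386 × 0.614/100) = 9.5 points. The picture does not change.

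**The case against.** Four points can fairly be made for the plan.

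- **The present sizing does not come from the pilot.** It uses a cited 66% and assumed rates of 45%, 50% and 55%. The article calls the calculation initial, calls the pilot effect size preliminary, and promises dedicated methods for clustered time-to-event outcomes. This stands: a reader might infer that the 600 patients were derived from pilot results, and they were not. The rule for finalizing the number is still stated in three places, and better formulas cannot repair an invalid input.
- **The pilot is not empty of control information.** A reader might infer that it can say nothing about the control rate. The article does not support that, because charts reach back to treatment initiation and MPACT came only after recruitment, so pre-MPACT periods exist. The article does not say that these would be used for sizing. Patients also had to be in treatment to enrol, so such histories are survivor-selected. A before-after contrast from them would be a weak preliminary effect, not a randomized one.
- **No harm is demonstrated.** A reader might infer that the sponsor will read the exposed rate as the control rate, or will cut the trial after an optimistic pilot. No section gives a re-estimation formula or a threshold for either, so neither outcome can be asserted.
- **The sizes rest on assumptions.** Constant hazard and the transfer of the trial's ICCs to two pilot clinics are not in the article. They serve as illustration, with the ranges shown.

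The difference in clocks, months of methadone treatment for the 66% against days from enrolment for the endpoint, belongs to the cited figure and would remain without any pilot. It matters here only for how a chart-based rate should be defined.

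**Conclusion.** The point holds in a limited form. The article assigns the pilot the tasks of determining a preliminary effect size, confirming a 12-month control rate and informing final sampling. The pilot's follow-up has no concurrent control, yields an exposed rate, and reaches 12 months only by extrapolation.

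Under constant hazard, the gap to be resolved at day 120 is 6.8 points, against a half-width of about 9 points with independence, 18 at ICC 0.05 and 24 at ICC 0.10. Other hazard shapes widen the 12-month range further. The structural part (no control, exposed rate, short horizon) needs no assumption. Only the sizes do.

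This should be corrected before final sampling is fixed. It does not show that the present sample size was derived from the pilot, or in which direction it would move.

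**What to change.** - In the Phase 2 Overview and the Discussion, remove the statements that the pilot determines the effect size for power or sets final sampling.
- Size the trial on a prespecified minimum worthwhile difference chosen on clinical grounds, not on what 30 clinics of 20 can detect. Report power at ICC 0.05 and 0.10. The choice of ICC matters: for 66% vs 50%, by the method of step 1 with design effect 1 + 19 × ICC, 600 patients give about 84% power at 0.05 and 68% at 0.10.
- In Statistical Analysis, do not let the pilot's MPACT-exposed rate confirm the 66%.
- If pilot charts inform the control rate, use only pre-MPACT periods, the trial's event definition, and a clock started at an index date in patients already in treatment. Report the result as a sensitivity range.
- Otherwise use the pilot for feasibility, data completeness and checks of the event definition.

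The cost is protocol wording plus a modest chart analysis if that option is taken. There are two downsides. Pre-MPACT histories of current patients are survivor-selected, which should be stated. Data Collection places missed doses in qualitative case notes, so extracting them takes some work.
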